### Statistical analyses

For our primary aim we will compare the proportion of successful abstainers in both groups, weekly (day 7, 14, 21) and after 3 months (primary outcome variable). Primary analyses are conducted with baseline and follow-up data according to the intention-to-treat approach. Secondly, we will compare the number of cigarettes smoked between the groups, controlling for baseline smoking (secondary outcome variable). Similar comparisons will be made for relationship satisfaction (secondary outcome variable). Additional independent and paired post-hoc t-tests will be performed to examine between-group and within-group differences, and chi-square tests for categorical variables*.* For the secondary aim, we will examine the effects of partner interactions on same and next-day smoking behaviour and relationship satisfaction (concurrent and lagged effects). Multilevel modelling will be used to analyse the diary data [29]. The diary data is nested within individuals and couples. Multi-level analyses will take into account between-person variation (individual variation from the grand mean) as well as within-person variation (an individual’s daily variation from their personal mean). To examine the indirect effect of the intervention on smoking and relationship satisfaction via partner interactions, we will conduct a within-person mediation analysis, allowing for random intercepts and slopes [29]. We will check whether the randomization was successful regarding demographical, smoking and relationship variables. If not, those variables will be taken into account as covariates in the analyses. 

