### Aims of the present study

The primary aim of this study is to assess immediate effectiveness and effectiveness over time of a dyadic planning intervention compared to an individual planning intervention for smoking cessation in smokers with a non-smoking partner. We hypothesize that participants in the dyadic planning condition will report fewer cigarettes smoked and a longer duration of abstinence than participants in the individual planning condition. We also hypothesize that participants in the dyadic planning condition will report higher relationship satisfaction than participants in the individual condition.

The secondary aim of this study is to examine possible underlying mechanisms in effectiveness in terms of partner interactions. We will examine differences between the conditions in the nature and frequency of partner interactions and how they are related to daily smoking behaviour and relationship satisfaction. We hypothesize that partners in the dyadic condition show more supportive behaviours in general and after a weak moment (of relapse), more often discuss weak moments, the plan, and the quit attempt. Additionally, we hypothesize that negative responses of the partner in the dyadic condition are less strongly related to a decrease in relationship satisfaction than in the individual condition.

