### Measures

Table 1 shows all variables that are measured (including exploratory/potential covariates).

**Table 1 Tab1:** Content of the baseline, diary and follow-up questionnaire

Measures	Baseline		Diary		Follow-up	
	*Smoker*	*Partner*	*Smoker*	*Partner*	*Smoker*	*Partner*
Baseline information						
Socio-demographics	X	X				
Smoking details and history	X	X			X	
Quit attempt history	X					
Primary & Secondary outcomes						
Number of cigarettes smoked	X		X	X	X	X
Hiding of smoking	X				X	
Duration of abstinence					X	X
Perceived frequency of smoking-related conflicts (SRC)	X	X			X	X
Relationship satisfaction	X	X	X	X	X	X
Smoking dependence	X		X	X	X	
Smoking now compared to before quit attempt					X	X
Mediators						
Details of partner contact			X	X		
Partner responses			X	X		
Partner responses to difficult moment			X	X		
Exploratory outcomes and potential covariates						
Attitude towards smoking	X	X				
Affect (PANAS)	X	X	X	X		
Opinion partner about quitting/smoking behaviour	X	X				X
Influence of SRC	X					
Perceived susceptibility	X	X			X	X
Perceived relatedness	X	X			X	X
Self-compassion towards relapse			X	X	X	X
Intention to quit	X				X	
Taking steps to go smoking			X			
Use of smoking replacement			X	X	X	X
Difficulty quitting			X	X		
Adherence to planning			X	X	X	X
Helpfulness of planning			X	X	X	X
Conflicts not related to smoking			X	X		
Interference of quitting with relationship			X	X		
Details social contacts			X	X		
Interference of quitting with social contact			X			
Other health behaviours	X	X				
SRC initiator	X	X				
SRC recentness	X	X				
SRC pattern	X	X				
Partner interaction questionnaire	X	X				
Details most difficult moment			X	X		
Distraction from smoking			X	X		
Motivation to remain quit			X			
Evaluation of diary			X	X	X	X
Self-efficacy to quit	X		X	X		
Daily activities			X	X		
Role of smoking in break-up					X	X
Influence of plan on relationship					X	X
Missing smoking					X	

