### Power analysis

In literature, 15.48% of the participants successfully quit smoking after an intervention using implementation intentions, measured one month later [3]. Therefore, we expect an abstinence rate of 15% in the individual planning (control) group. With a power of 0.8 and an alpha of .05, we need 70 couples per group to detect a relevant increase in effectiveness of 20% (primary aim). Additionally, we consider a minimal decrease of 50% in number of cigarettes, between baseline and follow-up, relevant [30].

A minimum sample of 50 cases is advised in a multi-level design [31] and diary studies in this research area are usually between 60 and 100 participants. Considering a power of .80 and an alpha of .05, the power analysis showed that a net sample size of 82 couples is sufficient to find an effect size of at least .3 (a medium effect) in the diary between smoking-related interactions and smoking behaviour (secondary aim). Therefore, with the sample of 140 couples we have sufficient power to detect a relevant difference in effectiveness of the intervention as well as the research questions related to the diary data. To take into account drop-out, we aim to include 15% extra couples.

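### The protocol contradicts itself on the primary time point: abstinence on days 7, 14, 21 and at 3 months shares one primary label, but primary analyses are limited to follow-up data

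*Protocol article*

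**What the plan says.** - **Statistical analyses, primary aim.** The plan states that "we will compare the proportion of successful abstainers in both groups, weekly" (days 7, 14 and 21) and after 3 months. A parenthetical tag at the end of that sentence marks the primary outcome variable.
- **Statistical analyses, next sentence.** "Primary analyses are conducted with baseline and follow-up data according to the intention-to-treat approach". The same section then ranks number of cigarettes and relationship satisfaction as secondary.
- **Primary outcomes.** The primary outcome is self-reported abstinence. No time point is given, and the daily diary question and the follow-up question are described together.
- **Aims of the present study.** The primary aim covers both the immediate effect and the effect over time. The hypothesis is that dyadic-planning participants "will report fewer cigarettes smoked and a longer duration of abstinence than participants in the individual planning condition".
- **Table 1.** The outcome rows sit under one heading, "Primary & Secondary outcomes", without ranking them.
- **Power analysis.** "With a power of 0.8 and an alpha of .05, we need 70 couples per group", for an increase of 20% over an expected 15% abstinent in the control group.

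**The concern.** Two consecutive sentences give different answers to which comparison decides the trial. The first puts four time points under one primary label. The second admits only baseline and follow-up (T2) data, and the day 7, 14 and 21 values come from the diary period (T1). The hypothesis adds a third version: it rests on cigarettes smoked, which the analysis section calls secondary, and on duration of abstinence.

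What is at stake is freedom of choice after the results are known. The protocol itself separates an immediate from a later effect, so the time points may disagree. As written, a difference on day 7 that has gone by 3 months could be presented as the primary result, and so could a difference seen only at 3 months. The error rate that the sample size assumes belongs to one test fixed in advance.

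**Working it through.** **1. Reproduce the planned sample size.** Inputs from Power analysis: control rate 15%; increase 20%, read as percentage points, so 35%; alpha .05; power 0.8. Sidedness is not stated; two-sided is assumed. The unpooled two-proportion formula gives

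n = (1.960 + 0.842)² × (0.15×0.85 + 0.35×0.65) / 0.20² = 7.849 × 0.355 / 0.04 = 69.66, rounded up to 70 per group.

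The stated 70 is therefore the size for one two-sided test at .05. The control rate comes from a study that measured abstinence at one month. That is none of the four time points, so the power section does not show which one is primary.

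**2. Set the statements side by side.**

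| Place | What it makes primary |
|---|---|
| Statistical analyses, first sentence | Proportion abstinent on days 7, 14, 21 and at 3 months |
| Statistical analyses, second sentence | Baseline and follow-up data only, hence 3 months |
| Primary outcomes | Abstinence, no time point |
| Aims, hypothesis | Cigarettes smoked and duration of abstinence |
| Power analysis | One comparison of proportions at .05 |

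The first two rows cannot both govern the primary analysis.

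**3. Size under the broader reading.** Suppose a difference at any of four tests, each at .05, could support a primary claim, and there is no true effect.

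- Independent tests: 1 − 0.95⁴ = 0.185. Bonferroni bound: 4 × .05 = 0.20. The same smokers are measured each time, so the true rate is lower.
- Equally correlated test statistics (simulated): 15.6% at correlation 0.5, 13.0% at 0.7, 11.4% at 0.8, 9.4% at 0.9.
- Cumulative abstinence (nobody returns to abstinent), 70 per arm, simulated under assumed rates on days 7, 14, 21 and at 3 months:

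| Assumed rates (%) | Chance of at least one significant test |
|---|---|
| 25 falling to 15 | about 10.5% |
| 30 / 25 / 22 / 15 | 11.3% |
| 40 / 30 / 25 / 15 | 12.4% |
| 50 / 35 / 28 / 15 | 13.4% |

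- Abstinence status that can change in both directions (latent correlation 0.8 down to 0.4): about 16–18%.

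Only the 15% comes from the document. The early rates and the correlations are assumptions.

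**4. Size under the narrower reading.** With the 3-month test alone, the false-positive rate is 5% and 70 per group is unchanged.

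**The case against.** The strongest reply is that the text already points to one test. The primary tag stands directly after the 3-month time point, the next sentence names baseline and follow-up data, and the sample size covers one comparison. On that reading nothing is inflated. It is a possible reading, but not the natural one. The matching secondary tags in the same section each label the whole comparison in their sentence, the Primary outcomes section describes diary and follow-up questions together, and the primary aim includes the immediate effect.

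A reader might infer that the trial may claim success on any of four tests. The document does not support that. It states no such rule, it gives alpha .05 only in the power section, and the follow-up sentence taken alone removes the diary days. A multiplicity procedure may also sit in an analysis plan that is not shown, so its absence here is not the point. The point is the contradiction, which an unseen document does not cure.

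A reader might also infer a loss of power. Under a Bonferroni split (.0125 per test), exact power of the 3-month test with 70 per arm would fall from 79.7% to 60.1%. But the protocol proposes no such split, and this is the power of one test, not the chance that at least one of four succeeds. It is not a defect of the plan.

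Two further replies carry weight. The loosely worded hypothesis does not by itself add primary tests, since the abstract and the analysis section both rank abstinence first. The Table 1 heading is only a grouping label. Neither one, however, resolves the conflict.

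**Conclusion.** Wrong as written: an internal contradiction. The protocol does not fix which abstinence comparison is primary, and its primary-aim hypothesis does not match the outcome it calls primary. The choice of primary result therefore stays open after the data are seen.

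The consequence depends on the reading. It is 5% if only 3 months counts, and about 10–18% with 70 per arm if any of the four comparisons at .05 could carry a primary claim. The upper range is conditional on that broader reading and on the assumed early abstinence rates and correlations. It is not the trial's established error rate.

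**What to change.** State that the proportion abstinent at the 3-month follow-up (T2) is the single primary outcome, tested at .05. This is where the follow-up sentence already points. Make days 7, 14 and 21 secondary: either test them only if T2 is significant, or report them as estimates with intervals. Align the Aims section as well. Word the primary hypothesis as the proportion abstinent at T2, and list the immediate effect, number of cigarettes and duration of abstinence as secondary. Changing the hypothesis alone would leave the immediate effect inside the primary aim.

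The cost is wording, together with a narrower primary aim. Sample size and alpha stay as planned. The downside is that a weekly difference on its own no longer supports a primary claim.

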### Randomization

Couples are randomized by the researchers by means of flipping a coin. Conditions are predetermined (before registration of the couple) by this method for every block of ten couples, to exclude any kind of influence the researchers might have. The randomization is single-blind; couples do not know that there are two different conditions until the debriefing that is given after the follow-up questionnaire. When participants do not fill in the follow-up questionnaire, the debriefing is sent to them by e-mail.

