#### Secondary outcomes

In the baseline and follow-up questionnaire, participants fill in the Dutch version of the Maudsley Marital Questionnaire [26, 27]. The scale contains 15 questions that are answered on 9-point Likert scales (e.g., ‘How much are you committed to this marriage?). Daily relationship satisfaction is measured by asking participants how satisfied they are with their relationship at that moment. The scale ranges from 1 = ‘Unhappy’ to 10 = ‘Very happy’.

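### Both members of each randomised couple rate relationship satisfaction at baseline and follow-up, but the plan provides for couple nesting only in the diary data; pooled or role-by-role testing would raise the false-positive risk for this secondary hypothesis.

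*Protocol article*

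**What the plan says.** All references are to the protocol article.

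- **Unit of randomisation** (Randomization): "Couples are randomized by the researchers by means of flipping a coin".
- **Who reports** (Measures, Table 1, titled "Content of the baseline, diary and follow-up questionnaire"): the row for relationship satisfaction is marked for smoker and partner alike at baseline, in the diary and at follow-up. Secondary outcomes agrees: "In the baseline and follow-up questionnaire, participants fill in the Dutch version of the Maudsley Marital Questionnaire".
- **Hypothesis** (Aims of the present study, under the primary aim): "participants in the dyadic planning condition will report higher relationship satisfaction than participants in the individual condition". No role is named.
- **Main comparison** (Statistical analyses): for smoking, "we will compare the number of cigarettes smoked between the groups, controlling for baseline smoking (secondary outcome variable"). The next sentence carries this over: "Similar comparisons will be made for relationship satisfaction (secondary outcome variable").
- **Supplementary tests** (same section): "Additional independent and paired post-hoc t-tests will be performed to examine between-group and within-group differences". They are not assigned to a particular outcome.
- **Clustering** (same section): multilevel modelling is assigned to the diary data, with the reason "The diary data is nested within individuals and couples". No such provision is made for the baseline and follow-up questionnaires.

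**The concern.** The number of cigarettes concerns one smoker per couple, so a plain between-group comparison suits it. Relationship satisfaction has two reports per couple. Carrying the same method over, with independent t-tests alongside, leaves open an analysis that counts two people rating the same relationship as two independent observations. Because arms are assigned to couples, the standard error of the arm difference must reflect variation between couples. A person-level test understates it whenever partners' scores are positively correlated.

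The other natural reading is to test smokers and partners separately. Each test is then valid, but a hypothesis that names no role can be declared supported by either.

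At stake is a stated hypothesis, that dyadic planning benefits the relationship. The Discussion says the results can be used to help couples maintain relationship satisfaction during a quit attempt, so a false positive would have consequences.

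**Working it through.** **Inputs**

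- n = 70 couples per group, alpha = .05, power 0.8 (Power analysis). Sidedness is not stated; two-sided is assumed. The alpha is given for the abstinence calculation and is taken here as the nominal level for this outcome too.
- Two reports per couple (Table 1).
- Within-couple correlation ρ: not given. **Assumed** 0.3 to 0.7, with lower values shown for reference.
- Equal means and variances in the two roles under the null are assumed for simplicity.

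**Step 1: the plan's own figure.** The article gives no sample size for relationship satisfaction. Its 70 per group is for abstinence, read as 15% versus 35%. With unpooled variances:

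(1.960 + 0.842)² × (0.15 × 0.85 + 0.35 × 0.65) / 0.20² = 69.66, so 70 per group.

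The figure reproduces, and it is a calculation with one outcome per couple.

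**Step 2: both partners pooled in an independent t-test.** Each arm mean averages 2n scores.

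- Variance of the arm difference that the test assumes: 2 × σ²/(2n) = σ²/n.
- True variance: 2 × σ²(1 + ρ)/(2n) = σ²(1 + ρ)/n.
- Ratio: 1 + ρ.
- Actual two-sided type I error: 2 × [1 − Φ(1.96/√(1 + ρ))].

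| Assumed ρ | 1 + ρ | 1.96/√(1 + ρ) | Actual type I error |
|---|---|---|---|
| 0.1 | 1.1 | 1.869 | 6.2% |
| 0.2 | 1.2 | 1.789 | 7.4% |
| 0.3 | 1.3 | 1.719 | 8.6% |
| 0.4 | 1.4 | 1.656 | 9.8% |
| 0.5 | 1.5 | 1.600 | 11.0% |
| 0.6 | 1.6 | 1.549 | 12.1% |
| 0.7 | 1.7 | 1.503 | 13.3% |

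An error of exactly 10% needs ρ = (1.960/1.645)² − 1 = 0.42.

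A simulation with 70 couples per arm and 20,000 runs per value gave 8.5%, 10.7% and 13.2% at ρ = 0.3, 0.5 and 0.7. A t-test on couple means, or on one role alone, stayed at about 5% throughout.

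**Step 3: the baseline-adjusted comparison.** The same expression applies approximately, with ρ replaced by the within-couple correlation of the residuals after adjustment for baseline. The article does not give that correlation either, so the table describes the unadjusted t-test and only indicates the mechanism for the main comparison.

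**Step 4: smokers and partners tested separately.** Each test holds 5%. The probability that at least one of two standard normal statistics with correlation ρ exceeds 1.96 in absolute value is 9.5%, 9.1% and 8.3% at ρ = 0.3, 0.5 and 0.7. The same simulation gave 9.4%, 9.0% and 8.2%.

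**The case against.** The strongest reply has four parts.

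1. **The t-tests are not the main analysis.** This stands. They are additional, post hoc and tied to no outcome, while the main comparison of relationship satisfaction follows a baseline-adjusted model. But that comparison has the same fault if both partners are pooled in it, so the fix must address it and not only the t-tests.

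2. **Pooling is not stated.** This also stands. The hypothesis on cigarettes and abstinence uses the same word for participants and must concern the smoker's behaviour, and the Power analysis counts couples throughout. However, Table 1 and Secondary outcomes have both members complete the questionnaire, and the relationship hypothesis is not limited to smokers. The options that avoid the problem are one prespecified role, a couple-level score or a model with couple clustering, and the text chooses none.

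3. **The correlation is unknown.** A reader might infer that the test rejects a true null about twice as often as stated. The article does not support that as fact: it needs pooling, which is not stated, and a correlation near 0.42, which is not given. Only the conditional range can be claimed.

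4. **A journal article may leave this to an analysis plan.** A fuller document may settle it. Yet Statistical analyses does more than stay silent. It names the tests, transfers a method from an outcome that concerns one person per couple, and confines couple nesting to the diary data. Followed literally, that leads to one of the two problems above.

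On role-by-role testing, it is fair to say that each test keeps its own 5% level and that the article does not say either result alone would support a claim. The 8% to 10% is therefore an error rate for the hypothesis as a whole, not a defect of either test.

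**Conclusion.** The point holds conditionally. The plan recognises couple nesting for the diary but makes no provision for it in the baseline and follow-up questionnaire, although both members of each randomised couple supply that outcome.

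- **Pooled as independent:** actual two-sided type I error of the unadjusted t-test about 8.6% to 13.3%, for an assumed ρ of 0.3 to 0.7. For the baseline-adjusted comparison the size depends on an unknown residual correlation.
- **Tested by role:** 5% per test, about 8% to 10% for at least one false positive on the one hypothesis.
- **One role fixed in advance, or one score per couple:** about 5%.

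A reader might also extend the concern to the primary outcome. That would be wrong: abstinence is the smoker's self-report, one outcome per couple. The diary analyses are also outside the point, since multilevel modelling is already planned for them. This should be corrected before analysis, but it does not threaten the primary conclusion.

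**What to change.** For the main baseline-adjusted comparison of follow-up relationship satisfaction, and for any supplementary between-group test of it, specify one mixed model on both partners' scores:

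- fixed effects for arm, role (smoker or partner), arm-by-role and own baseline score;
- a random couple effect, or role-specific errors correlated within couple;
- the overall arm effect, averaged over the two roles, as the single test of the hypothesis;
- role-specific effects reported descriptively.

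A couple mean or one prespecified role would also hold 5%. The mixed model has the advantage of using both reports and showing the two roles separately.

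**Cost:** a change of analysis wording only. The data are already collected under Table 1, and multilevel modelling is already planned for the diary. The downside is somewhat wider, correct confidence intervals. Relative to an unadjusted analysis that pools partners as independent, the factor is √(1 + ρ), from √1.3 = 1.14 to √1.7 = 1.30 over the assumed range.

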#### Mediators

Daily partner interactions (supportive behaviours and negative responses) will be examined as a possible mediator in the relationship between the intervention and the primary outcomes. First of all, participants are asked whether they had contact with their partner today (e.g., talking, texting). If they had contact, they are asked how satisfied they are about this (1 = ‘Not at all’ to 7 = ‘Very much’). Details are asked about the time spent with the partner (e.g., how much time, when during the day). Supportive behaviours and negative responses are measured by seven questions about interactions about smoking and the planning (e.g., today my partner motivated me to remain abstinent, today my partner did not show interest in my planning, today my partner and I had a fight about my planning). The answer scale ranges from 1 = ‘Not at all’ to 7 = ‘Very much’. Participants are asked whether they discussed the most difficult moment of that day with their partner, and if so how he/she responded. Partner responses (supportive and negative) to difficult moments are measured by four items (i.e., supportive, motivating, angry/irritated, blaming) and participants are asked to score these on a scale from 1 = ‘Not at all’ to 7 = ‘Very much’.

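### The baseline Partner interaction questionnaire can enter the secondary-aim models only through an arm-imbalance check, which is the wrong trigger for both precision and confounding

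*Protocol article*

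**What the plan says.** All references are to the protocol article.

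- **The aim.** Under Aims of the present study, the secondary aim includes an arm comparison: "We will examine differences between the conditions in the nature and frequency of partner interactions". It also covers how these interactions relate to daily smoking and relationship satisfaction.
- **The mediator.** Under Mediators: "Daily partner interactions (supportive behaviours and negative responses) will be examined as a possible mediator". It is measured in the diary, after the intervention.
- **The baseline measure.** Table 1 under Measures has a row "Partner interaction questionnaire", marked for smoker and partner at baseline and at no later time. It stands in the block "Exploratory outcomes and potential covariates".
- **The secondary-aim models.** Statistical analyses states: "For the secondary aim, we will examine the effects of partner interactions on same and next-day smoking behaviour and relationship satisfaction". It adds: "Multi-level analyses will take into account between-person variation (individual variation from the grand mean) as well as within-person variation". For the indirect effect, "we will conduct a within-person mediation analysis, allowing for random intercepts and slopes". None of these sentences names a baseline partner-interaction term.
- **Baseline adjustment that is planned.** "Secondly, we will compare the number of cigarettes smoked between the groups, controlling for baseline smoking (secondary outcome variable"; the same kind of comparison is promised for relationship satisfaction.
- **All other baseline variables.** The section ends with a check of whether randomisation succeeded on demographic, smoking and relationship variables. Variables on which it did not succeed become covariates.

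**The concern.** The only stated route for the questionnaire into the secondary-aim models is observed arm imbalance. That trigger fails in two ways.

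1. **Precision.** The value of a baseline covariate in a randomised comparison comes from its correlation with the outcome, not from chance imbalance. If the arms look alike, the rule leaves the covariate out and the precision is lost.
2. **Confounding of a non-randomised exposure.** Condition is randomised, but partner interaction during the diary is not. Couples who were already supportive may report more diary support and also smoke less, or be more satisfied, for other reasons. A check of balance between arms says nothing about this.

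The article's own Background makes the second possibility plausible. It cites work in which partner support before as well as during a quit attempt was related to less smoking, and in which intended support was higher among more satisfied partners. The stakes are the mechanism claim. The Discussion proposes that interactions found to help abstinence could be advised in cessation interventions.

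**Working it through.** **The plan's own figures.** A two-sided 5% test of a correlation of 0.3, using the noncentral t with n − 2 degrees of freedom, needs 82 couples (power 80.3%). This matches the Power analysis section. For 15% v 35% abstinence, the unpooled normal formula gives 69.7, so 70 per group, which also matches. Neither figure is in dispute.

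**Inputs.** From the documents: 70 couples per arm, alpha .05 (taken as two-sided), power .80. Assumed, because the documents give none: the correlation ρ between the baseline score and couple-mean diary interaction, and the correlation of the baseline score with the outcome.

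**(a) Arm comparison of diary interactions.** Adjustment multiplies the residual variance by (1 − ρ²).

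- Detectable difference, unadjusted: (1.960 + 0.842) × √(2/70) = 0.474 SD. Adjusted: 0.474 × √(1 − ρ²).
- Power for 0.40 SD: Φ(0.40 / [√(1 − ρ²) × √(2/70)] − 1.960). With ρ = 0 this is Φ(2.366 − 1.960) = 65.8%.

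| ρ | detectable difference (SD) | power at 0.40 SD |
|---|---|---|
| 0 | 0.474 | 65.8% |
| 0.2 | 0.464 | 67.6% |
| 0.3 | 0.452 | 69.9% |
| 0.5 | 0.410 | 78.0% |
| 0.7 | 0.338 | 91.2% |

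The t distribution gives figures about one point lower (65% and 77% at ρ = 0 and 0.5). The 0.40 SD is illustrative and is not a planned effect.

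**(b) Between-couple association and mediator-outcome path.**

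*Which part is exposed.* The models split interactions into deviation from the grand mean and daily deviation from the personal mean. A stable level of prior support cancels from the second and remains in the first. Condition varies only between couples, so its indirect effect must run through couple-level support, where prior support can act.

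*How large it could be.* Suppose diary support has no effect, the baseline score correlates ρ with diary support, and it correlates q with the outcome. The spurious couple-level correlation is ρ × q. With 140 couples and Fisher's z, the chance of a false positive is about Φ(atanh(ρq) × √137 − 1.960):

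- ρ = 0.5, q = 0.3: correlation 0.15, about 42%.
- ρ = 0.5, q = 0.2: correlation 0.10, about 22%.
- ρ = 0.3, q = 0.2: correlation 0.06, about 11%.

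In the other direction, an observed correlation of 0.30 with ρ = 0.5 and q = 0.2 becomes (0.30 − 0.10) / √(0.75 × 0.96) = 0.24 after adjustment.

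*What adjustment costs here.* The covariate is correlated with the predictor under test. At ρ = 0.5 the standard error grows by 1/√(1 − 0.25) = 1.155, about 15%. If prior support acts only through diary support and the true correlation is 0.3, then q = 0.15 and the partial correlation is (0.30 − 0.075) / √(0.75 × 0.9775) = 0.263. Power then falls from 80% to 68% at 82 couples, and from 96% to 89% at 140.

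**The case against.** The strongest reply is that the article is condensed, no analysis plan is shown, and which potential covariates enter which model is commonly left to that plan. This defeats any claim of a proven omission. It does not defeat criticism of the covariate rule, which the article does state and which uses the wrong trigger for this purpose.

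A reader might infer several stronger things that the documents do not support:

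- *That the questionnaire will never be used.* Table 1 lists it with potential covariates, and it could count as a relationship variable under the imbalance rule. It has a conditional route, but no planned one.
- *That the arm comparison is biased.* Randomisation keeps it unbiased. The loss is in precision only, and is small if ρ is 0.3 or less.
- *That the daily associations are confounded by prior support.* The same-day and next-day effects are a main target of the quoted sentence. Stable prior support drops out of them once they are centred on the personal mean.
- *That confounding of the between-couple part is shown.* It is possible, not demonstrated. The false-positive rates above follow from correlations that were assumed, and they describe a couple-level test rather than the full multilevel model. The article also does not say that it will read the between-person coefficient causally.
- *That the questionnaire is a baseline version of the mediator.* Its content is not described, and some diary items concern a plan that does not exist at baseline. Table 1 also lists other baseline items that bear on negative interactions, such as smoking-related conflicts. A weak correlation is quite possible.
- *That adjustment is nearly free everywhere.* That is true of the arm comparison only. In the support-outcome models it costs power, as shown above.

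**Conclusion.** The point holds in a limited form. The article collects a pre-intervention partner-interaction score from both partners and leaves its use to an imbalance check that serves neither purpose for which the score is useful.

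For the arm comparison, prespecified adjustment is better than the stated rule. At 70 couples per arm and 0.40 SD it adds about 4 points of power at ρ = 0.3 and about 12 at ρ = 0.5. For the between-couple association and the mediator-outcome path, the score addresses a plausible rival explanation that arm balance cannot exclude, at a real price in power. All sizes rest on assumed correlations. The within-person daily and lagged effects and the stated sample sizes stand as they are.

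**What to change.** In Statistical analyses, make two additions.

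1. **Arm comparison of diary partner interactions.** Enter the respondent's own baseline Partner interaction questionnaire score as a prespecified covariate, whether or not the arms look balanced. The cost is one degree of freedom and one sentence, from data already collected. If the score correlates weakly with the diary items, little is gained and little is lost.
2. **Models with a between-person partner-interaction term, and the mediator-outcome path.** Report the estimate adjusted for this score beside the unadjusted one, and state that the unadjusted between-person coefficient is not interpreted as an effect of support. The cost is a wider interval for the adjusted estimate (standard error about 15% larger at a correlation of 0.5) and hence lower power for the between-couple association. Showing both estimates lets the reader see this trade-off.
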